### Randomization and Blinding

Thirty minutes before ACC release, the enrolled participants who meet the eligibility criteria will be randomly allocated in a 1:1 ratio to 2 groups, namely, group A (treated with amiodarone) and group P (placebo control). Block randomization will be used with a block size of 4, which will be implemented with SPSS (version 22.0; IBM Corp) by an independent statistician, and the randomization numbers will be given to an external data manager with no involvement in the study procedures and concealed on password-protected computer.

When a patient meets the eligibility criteria, the external data manager will return the corresponding allocation to the nurse anesthetist. The drugs will be prepared by the nurse anesthetists according to the allocation information, packaged with the same looking and labeled with numbers, and injected by the anesthesiologists. Both anesthesiologists and patients will be blinded to the regimen. The anesthesiologist will be notified of the study group by the nurse anesthetists in case of emergency. However, the nurse anesthetists have no role in assessing the treatment actions, analyzing, or interpreting the data.

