### Interventions

#### Treatment Regimen of Amiodarone

Thirty minutes before ACC release, the trial drugs will be administered through the central venous line. In group A, 150 mg of amiodarone will be diluted to 20 mL normal saline and pumped in 5 minutes. In group P, 20 mL normal saline will be pumped in 5 minutes (Table 1).

**Table 1 table1:** Schedule for enrolment and intervention per cluster.

Time point^a^		Enrollment	Allocation	Close-out			
		–*t*_1_	0	*t* _1_	*t* _2_	*t* _3_	*t* _4_

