**Assessments**							
	Baseline demographic information	✓					
	Primary end point^e^				✓		
	Secondary end point^f^				✓	✓	✓

^a^Time point: *t*_1_: baseline; *t*_1_: intervention period, 30 minutes before aortic cross-clamp (ACC) release; *t*_2_: 10 minutes after ACC release; *t*_3_: 15 minutes after weaning from cardiopulmonary bypass; *t*_4_: the end of surgery.

^b^✓: refers to crucial events at corresponding points in time.

^c^Group A: amiodarone group.

^d^Group P: placebo-controlled group.

^e^Primary end point: occurrence of ventricular fibrillation (VF).

^f^Secondary end point: *t*_2_: the number and maximum energy of defibrillations to terminate VF; *t*_3_: heart rate, mean arterial pressure, mean pulmonary arterial pressure, central venous pressure; *t*_4_: the total dosages of vasoactive agents.

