### End Points

The primary end point is the incidence rate of VF 10 minutes after ACC release. The secondary end points include the duration of VF, the number and maximum energy of defibrillations needed to terminate VF, the use of other antiarrhythmic agents, and epicardial temporary pacemakers after ACC release. Besides, the secondary end points also include heart rate, MAP, mean pulmonary arterial pressure, central venous pressure and CI 15 minutes after anesthetic induction and weaning from CPB, and the speed of vasoactive agents at the end of CPB and surgery and their total dosages.

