### Statistical Analysis

All data will be analyzed using SPSS (version 22.0; IBM Corp) and in accordance with the intention-to-treat principle, beginning immediately after randomization. All statistical tests will be considered significant if *P*<.05. Only 2-sided tests will be used. Baseline characteristics will be described and compared by using the Fisher exact test for the categorical variables and 2-sample *t* test or Wilcoxon rank sum test depending on the normality of the data distribution for the continuous variables. The continuous variables will be described by mean and SD values if normally distributed or median and interquartile range if not. The normality of distributions will be checked graphically and using the Kolmogorov-Smirnov test. If there is a violation of distribution assumption, appropriate transformation will be used. The categorical variables will be expressed as frequencies and percentages.

For the primary end point, the incidence rate of VF 10 minutes after ACC release will be compared by using the chi-square test. For the secondary end points, heart rate, MAP, mean pulmonary arterial pressure, central venous pressure, and CI will be compared between 2 groups by using a repeated measures ANOVA model during the 2 observation times. Other continuous secondary end point variables will be compared between 2 groups by using a 2-sample *t* test or a Wilcoxon rank sum test depending on the normality of the data distribution. The chi-square test or Fisher exact test will be used to compare categorical secondary end point variables.

If data are missing at random, the analyses will be carried out using multiple imputations. The multiple imputation procedure will be based on all available data for that patient and be conducted using the chained equation approach. If data are not missing at random, the analyses will be conducted using available data with appropriate interpretational reservations. We will also evaluate the data using the intention-to-treat principle and per-protocol data set and compare the analysis results to estimate reliability of our analytical results.

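### The repeated measures ANOVA for the hemodynamic end points treats a pre-randomisation baseline as an outcome and does not name the tested term; ANCOVA on that baseline is as efficient or better under either reading

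*Protocol article*

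**What the plan says.** Under Statistical Analysis, the protocol article lists five hemodynamic variables (heart rate, mean systemic and mean pulmonary arterial pressure, central venous pressure, cardiac index) that will be "compared between 2 groups by using a repeated measures ANOVA model during the 2 observation times". It names neither the group main effect nor the group-by-time term as the test, and no covariate.

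End Points supplies the two times: "central venous pressure and CI 15 minutes after anesthetic induction and weaning from CPB".

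Randomization and Blinding places allocation later than the first of these: "Thirty minutes before ACC release, the enrolled participants who meet the eligibility criteria will be randomly allocated". Treatment Regimen of Amiodarone gives the same time for the drug: "Thirty minutes before ACC release, the trial drugs will be administered through the central venous line".

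Footnote f of Table 1 lists, at the post-weaning time only, "heart rate, mean arterial pressure, mean pulmonary arterial pressure, central venous pressure". It does not list cardiac index there, and the table shows no hemodynamic measurement after induction.

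**The concern.** By the order of events under Anesthesia Protocols and Surgical and CPB Procedures, induction comes first. Line placement, sternotomy, cannulation and bypass follow, and only then the period before cross-clamp release in which patients are allocated and dosed. The post-induction value cannot carry a treatment effect. Any group difference in it is chance.

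A two-group, two-time repeated measures ANOVA offers two terms that could serve as the comparison. The group main effect compares the groups on the average of both times, so it mixes the post-weaning effect with a known zero. The group-by-time term compares the changes. The two answer different questions with very different power, and the article leaves open which one counts.

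The hemodynamic state after weaning is the second aim under Objective, so a diluted test would weaken the answer to a stated question of the trial.

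**Working it through.** **Inputs from the article.** Two times, one before and one after randomisation (End Points; Randomization and Blinding); 1:1 allocation; two-sided testing at 0.05 (Statistical Analysis); 27 recruited per group, 21 before the dropout allowance (Sample Size Estimation).

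**Assumed, because the article does not give them.** Equal SD σ at the two times; correlation r between them, varied from 0 to 0.8.

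**The plan's own figure.** No power is stated for the hemodynamic end points. The group size can be reproduced from the primary end point: (1.960 + 0.842)² × (0.7×0.3 + 0.3×0.7) / 0.40² = 20.6, so 21; then 21/0.8 = 26.25, so 27. It is used below only as the group size.

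**Expected estimates.** Let δ be the true post-weaning difference.
- Group main effect: (0 + δ)/2 = δ/2. This holds whatever the SDs and r.
- Group-by-time: δ − 0 = δ.
- ANCOVA on the post-induction value: δ.

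**Signal relative to a t test on post-weaning values alone (set to 1).**
- Group main effect: the average of the two times has SD σ√((1+r)/2), so the ratio is 0.5/√((1+r)/2) = 1/√(2(1+r)).
- Group-by-time: the change has SD σ√(2(1−r)), so the ratio is 1/√(2(1−r)).
- ANCOVA: the residual SD is σ√(1−r²), so the ratio is 1/√(1−r²).

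Group-by-time divided by ANCOVA is √((1+r)/2), which never exceeds 1.

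**Power.** The reference is the effect that the post-only t test detects with 80% power, 0.777 SD at 27 per group. Noncentral t results, in percent:

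| r | Group main effect | Group-by-time | ANCOVA |
|---|---|---|---|
| 0 | 50.8 | 50.8 | 80.0 |
| 0.2 | 44.0 | 60.1 | 81.5 |
| 0.3 | 41.2 | 65.8 | 83.5 |
| 0.5 | 36.6 | 80.0 | 89.9 |
| 0.7 | 33.0 | 95.1 | 97.5 |
| 0.8 | 31.4 | 99.3 | 99.7 |

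Hand check at r = 0.5 by the normal approximation: the ratio is 0.5/√0.75 = 0.577, and Φ(2.80 × 0.577 − 1.96) = Φ(−0.34), about 37%. A simulation of 20,000 trials at r = 0.5 with 27 per group gave 36.5% for the main effect, 80.1% for group-by-time and 79.8% for the post-only test. With 21 per group, where the 80% reference effect is 0.886 SD, the powers agree to within 0.1 point.

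**Sample size equivalent.** To match the post-only test, the main effect needs 2(1+r) times as many patients: 2 times at r = 0, 3 times at r = 0.5, 3.6 times at r = 0.8.

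**The case against.** The strongest reply is that the article does not commit to the main effect. The group-by-time term of the same model is valid and undiluted, and above r = 0.5 it beats a post-only comparison. Which term is tested is a detail that a condensed article may leave to an analysis plan that is not shown. This stands to the extent that dilution cannot be asserted as certain. It does not remove the point: the article fixes a model in which a baseline is an outcome, its phrase about comparing two groups most naturally means the main effect, and group-by-time is still no more efficient than ANCOVA. If group-by-time is meant, what remains is a matter of efficiency and not an error.

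A reader might infer that the test loses most of its power. The documents do not support that in general, because they give no correlation. More than half of the 80% is lost only if r exceeds about 0.35 against a post-only test, or about 0.26 against an ANCOVA with 80% power. One value precedes bypass and the other follows cardioplegia, hypothermia and titrated vasoactive support, so a high correlation cannot be presumed.

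A reader might also infer that the trial will publish a halved estimate. The article does not say that a time-averaged difference will be reported, and group summaries at each time would fit its text.

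Finally, Table 1 might be read as showing that the baseline data will not be collected. Footnote f is visibly abridged: it also leaves out VF duration, pacing and vasoactive infusion speed. End Points lists both times and cardiac index, so the measurements are planned and the two places only need reconciling.

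**Conclusion.** The point holds in a conditional form. It is certain from the text that one of the two analysed times precedes randomisation and that the tested term is not named. If the group main effect is the test, the expected estimate is exactly half the post-weaning difference, and 80% power falls to between about 51% and 31% for r from 0 to 0.8. If group-by-time is the test, it is valid, with a shortfall against ANCOVA of about 18 points at r = 0.3 and 10 points at r = 0.5, and almost none at 0.8.

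The halving needs no assumption. The power figures rest on equal SDs, non-negative correlation and an effect sized for 80% power in a post-only test; they would shift if the spread before and after bypass differs. Only secondary end points are concerned. The comparison of VF incidence and the sample size built on it are untouched.

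**What to change.** Replace the repeated measures ANOVA sentence with: each hemodynamic variable measured 15 minutes after weaning will be analysed by ANCOVA, with treatment as factor and the post-induction value of the same variable as covariate, and the adjusted mean difference will be reported with its 95% confidence interval. Write confidence interval and cardiac index in full, since the article abbreviates cardiac index as CI.

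Add the post-induction hemodynamic measurement and cardiac index to Table 1 so that it agrees with End Points.

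The cost is one sentence and two table entries. Both measurements are already listed as end points, so no further patients or assessments are needed. The change should be recorded before any unblinded comparison; the article reports 21 of 54 participants recruited.

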### Adverse Events Observation

During trial agent infusion, if the mean arterial pressure is less than 50 mm Hg, 20-40 μg of norepinephrine will be administered through the CPB venous reservoir. After recovery of the autonomous cardiac rhythm, if the heart rate is <60 bpm or a type II second-degree or third-degree atrioventricular block develops, 0.5-1 mg of atropine will be used intravenously, and if it does not work, epicardial temporary pacing will be performed. If the QT interval is >440 milliseconds or the corrected QT interval is >400 milliseconds, 0.5-1 mg of atropine will be given to increase heart rate to >70 bpm and blood potassium will be ensured at >4.0 mmol/L.

### Data Collection and Management

The data will be collected from paper case report forms (manually counter checked with source files by the data entry personnel) by the investigator and given to the statistician to analyze the data. The data will be recorded by their specific ID number instead of participant’s name throughout the study unless otherwise specified. Access to data will be restricted to the investigators who signed the confidential disclosure agreement or to the institutional or governmental auditors during the study. All original documents and files will be archived for at least 5 years to allow inspection after the trial has ended. The process will be monitored by the Institutional Ethics Committee of the First Affiliated Hospital of Nanjing Medical University.

### Ethical Considerations

This study has been approved by the Institutional Ethics Committee of the First Affiliated Hospital of Nanjing Medical University (2020-SR-175) and registered with the Chinese Clinical Trial Registry (ChiCTR2000035057). Informed consent will be obtained from all participants before recruiting to the study.

## Results

The study began in August 2022, and the data collection will take place for the next 2 academic years. To obtain the total study sample, a total of 54 participants will be recruited. At present, 21 participants have already been recruited for the study.

## Discussion

The clinical trial is designed in order to investigate the efficacy of prophylactic intravenous amiodarone administration on reperfusion VF after release of ACC in patients with LVH undergoing CPB surgery.

Reperfusion VF is a common arrhythmia encountered after ACC release in patients undergoing CPB surgery. Repeated defibrillation and long duration of VF could increase myocardial oxygen consumption, damage cardiomyocytes, and decrease the patients’ prognosis postoperatively. In patients with LVH, cardiac protection is often not as effective as the normal heart during CPB, and thus reperfusion VF is easier to occur and more difficult to be terminated.

Amiodarone, known as class III antiarrhythmic agent, has the properties of converting VF and restoring the sinus rhythm and can also be administered in patients with structural heart diseases. Before ACC release, administration of amiodarone has been confirmed useful to reduce occurrence of reperfusion VF. However, few proofs supported the effect of amiodarone before ACC release on reducing VF in patients with LVH. With this trial, we are hoping to further demonstrate that prophylactic infusion of amiodarone could reduce the occurrence of reperfusion VF in patients with LVH.

The limitation of this study may include the following aspects. First, this is a single-center trial with Asian patients in which there might be a selection bias. Second, the sample size is relatively small. However, according to the clinical experience in our center, the incidence of reperfusion VF is similar to those documented in the literature. So, the sample size could prove our hypothesis. We hope that in the future, a multicenter clinical trial with larger sample size could be performed to further elucidate this problem.

This study is believed to provide more proof regarding how to avoid reperfusion VF in patients with LVH undergoing CPB surgery, reducing myocardial damages occurred in those patients.

## Abbreviations

ACC: aortic cross-clamp
BIS: bispectral index
CI: cardiac index
CK-MB: creatine kinase-myocardial band
CPB: cardiopulmonary bypass
LVH: left ventricular hypertrophy
MAP: mean arterial pressure
VF: ventricular fibrillation
